### Data collection

Balance and mobility will be assessed at baseline, two weeks and at three months after randomisation. Self reported physical functioning will be assessed at two weeks and at three months after randomisation. Information about falls and hospital readmissions will be collected at two weeks and at three months after randomisation. A proxy will be used for assessment of self reported physical functioning and fall/hospital readmission data if the assessor had significant concern over the reliability of information collected from the participant. Blinded assessors (experienced therapists) will conduct follow-up assessments.

Pre-morbid level of functioning (whether the participant could climb a flight of stairs and walk 800 m in the three months prior to hospital admission) and 12-month fall history will be collected during the baseline assessment. Medical records will be extracted to determine presenting diagnosis and demographic data.

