### Participants

All patients admitted to the adult general rehabilitation ward at Bankstown-Lidcombe Hospital will be screened for study eligibility. Patients will be eligible if they are: admitted to the ward for rehabilitation; are able to stand for 30 seconds without physical assistance or the help of an assistive device; have no contraindications to exercise, such as uncontrolled hypertension or unstable cardiac disease; are able to fully weight bear as ordered by a medical officer; and are suitable for a group exercise class with minimal supervision as determined by the treating physiotherapist. Patients with a known multi-resistant organism infection or other infection that would pose a significant risk to others in a group setting (e.g. Methicillin-Resistant Staphylococcus Aureus, Vancomycin Resistant Enterococci, Tuberculosis) will be excluded.

Patients with a Mini Mental State Examination (MMSE) score of more than 17 will be asked to give informed consent to study participation. Consent will be sought from a ‘person responsible’ for patients who score 17 or less on the MMSE as well as for individuals who score more than 17 but treating staff consider to have a cognitive impairment that would hamper the ability to give informed consent. Interpreters will be used for consent and study assessments as required.

The South West Sydney Local Health District Human Research Ethics Committee (HREC) approved the study protocol (HREC/10/LPOOL/187).

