#### Secondary outcomes

Secondary outcomes will include mobility, self reported physical functioning, fall incidence and hospital readmissions.

Mobility will be assessed using the lower extremity Summary Performance Score [20] version of the Short Physical Performance Battery [21]. This battery gives a composite score based on timed performance of three mobility tasks: the ability to stand up for 10 seconds with feet in different positions (together side by side, semi-tandem and tandem), 4-metre walk and time to rise (stand-up) from a chair five times.

Self reported physical functioning will be assessed using the Basic Mobility and Daily Activity domains of the Computer Adaptive Testing version of the Boston University Activity Measure for Post Acute Care (AM-PAC) (Haley et al. 2004) [22]. Computer Adaptive Testing uses a computer algorithm to pre-select the items that will be administered to a specific patient based on their responses to previous items. The AM-PAC measures functional outcome by using Item Response Theory (IRT). The AM-PAC Basic Mobility domain includes 101 items that address basic movement and physical functioning activities, such as bending, walking, carrying and climbing stairs. The AM-PAC Daily Activity domain includes 70 items that address basic self-care and instrumental activities of daily life.

Information about falls and hospital readmissions will be collected via interview at two-weeks and at three-months and confirmed via hospital records data.

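### Falls after discharge that never reach hospital rest on recall at one interview covering about 11 weeks; a dated calendar would lose fewer of them

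*Protocol article*

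**What the plan says.** All references are to the protocol article, Methods/Design.

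- **Status of the outcome.** Secondary outcomes: "Secondary outcomes will include mobility, self reported physical functioning, fall incidence and hospital readmissions".
- **Source of the data.** The same section continues: "Information about falls and hospital readmissions will be collected via interview at two-weeks and at three-months and confirmed via hospital records data". Data collection repeats the two time points. No interview between them, and no diary or calendar, is described.
- **Who answers.** Data collection: "A proxy will be used for assessment of self reported physical functioning and fall/hospital readmission data", on the condition "if the assessor had significant concern over the reliability of information collected from the participant". No score threshold is given, and nothing asks for the same respondent at both visits or for a record of who answered.
- **Who can be enrolled.** Participants sets no cognitive exclusion. Consent comes from a person responsible "for patients who score 17 or less on the MMSE", and also for higher scorers whom treating staff consider too impaired to consent.
- **Who assesses.** Data collection: "Blinded assessors (experienced therapists) will conduct follow-up assessments".

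**The concern.** Most of the follow-up time falls between the two interviews, and for many participants much of it will be spent out of hospital. A fall at home with no hospital contact can enter the data only if someone remembers it and reports it at three months. The sample can include people whose recall may be poor, and the proxy safeguard operates only once the assessor doubts the answers given.

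Checking against hospital records does not close this gap. Records can verify a fall that led to hospital contact, but they cannot show one that did not.

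At stake is the fall comparison. The Background and Discussion rest much of the trial's rationale on falls, so a comparison weakened by missed events would make a benefit harder to see and, equally, a harm.

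**Working it through.** The plan gives no fall rate, readmission rate or capture figure, so there is no figure of its own to reproduce on this point.

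**1. Length of the recall window.** Three months = 3 × 365.25 / 12 / 7 = 13.04 weeks. Less two weeks, this leaves 11.04 weeks. The share of follow-up covered by the second interview is 11.04 / 13.04 = 85%. This is the time one interview covers, not the share of events resting on recall alone, because hospital events also have a records source.

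**2. Which events depend on recall.** Setting Secondary outcomes beside Data collection:

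| Event | Interview | Hospital records |
|---|---|---|
| Readmission | yes | yes |
| Fall in hospital, or fall leading to hospital contact | yes | yes, if recorded |
| Fall after discharge without hospital contact | yes | no |

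Only the last row rests on recall alone. The article's wording also suggests that records are used to check reported events rather than to search for unreported ones. Even a full search would not change the last row.

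**3. What missed falls would cost (illustration).**

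Inputs from the article: total sample 162 and drop-out 15% (Sample size calculation); dichotomous outcomes analysed by logistic regression (Statistical analysis). With 1:1 allocation assumed, the number analysed per arm is n = 162 × 0.85 / 2 = 68.85.

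Assumptions, none of them from the article: the fall outcome is analysed as the proportion with at least one fall; a share s of true fallers is captured, the same in both arms; there are no false reports; the test is two-sided at 0.05.

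The observed proportions are s·p₀ and s·p₁. Writing these as q₀ and q₁, with mean q̄:

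power = Φ{ [ |q₀ − q₁| − 1.96·√(2q̄(1 − q̄)/n) ] / √( [q₀(1 − q₀) + q₁(1 − q₁)]/n ) }

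For true proportions of 40% and 20%:

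- s = 1: (0.200 − 1.96 × 0.0781) / 0.0762 = 0.62, power 73%
- s = 0.8: (0.160 − 1.96 × 0.0728) / 0.0715 = 0.24, power 60%
- s = 0.6: (0.120 − 1.96 × 0.0655) / 0.0647 = −0.13, power 45%

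Over a range of assumed proportions:

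| True proportions | Full capture | 80% captured | 60% captured |
|---|---|---|---|
| 30% v 15% | 56% | 45% | 34% |
| 40% v 24% | 52% | 40% | 30% |
| 40% v 20% | 73% | 60% | 45% |
| 50% v 30% | 67% | 52% | 38% |

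**4. What happens to the estimate.** The risk difference shrinks in proportion to s: 20 percentage points becomes 0.6 × 20 = 12. The odds ratio moves toward 1, from (0.20/0.80)/(0.40/0.60) = 0.375 to (0.12/0.88)/(0.24/0.76) = 0.432. The risk ratio stays at 0.5, with less precision. Equal capture in both arms therefore gives attenuation and noise, not a spurious effect.

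**The case against.** The case on the other side is substantial, and several stronger readings do not survive it.

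- **That 85% of follow-up rests on recall alone.** A reader might infer this from the interview schedule. The article says interview data are confirmed from hospital records, so the point has little force for readmissions or for falls that reach hospital.
- **That the proxy rule biases the comparison between arms.** The person who invokes it is blinded. Blinding does not stop the choice of respondent from depending on the participant's condition after randomisation, but nothing in the article gives that path a direction or a size.
- **That a change of respondent would appear as change in self-reported function.** Statistical analysis compares groups at each follow-up, and Data collection lists this measure only at two weeks and three months. Change between those visits is not a stated outcome.
- **That the number of low MMSE scorers measures the problem.** The article gives no MMSE distribution, and the requirement of suitability for a group class may limit low scorers. The proxy rule is not tied to the MMSE and applies to everyone.
- **That the respondent should be fixed by consent status.** Capacity to consent is not the same as ability to report a fall. Such a rule would impose proxies on some who can answer, and nothing shows that the person who consents sees the participant's daily life.

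It can also be said that the proxy provision is itself a safeguard, and that a condensed article may leave recall aids to a fuller document. Both are fair. The text is neither false nor contradictory, and the absence of a recall aid from the article does not prove that none is used. What remains is that the method as described, two interviews about 11 weeks apart backed by records, cannot recover unremembered falls without hospital contact.

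**Conclusion.** The point holds in a limited form, as a worthwhile improvement to one secondary outcome. Falls after discharge without hospital contact depend on recall over up to about 11 weeks, in a sample that may include cognitively impaired patients, and some can be missed. How many is unknown.

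Under the assumed rates above, capturing 80% of fallers costs about 11 to 15 percentage points of power, and capturing 60% costs about 22 to 29. These figures illustrate the mechanism and are not estimates for this trial. They rest on equal capture in the two arms, which assessor blinding makes reasonable but does not guarantee. The documents support attenuation and lost precision in the fall comparison; they do not demonstrate bias between arms. The primary outcome, timed standing balance measured directly by the assessor, is unaffected.

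**What to change.** 1. Give each participant a dated fall and hospital-contact calendar. Where the participant cannot complete it, give it to a carer or proxy. Work through it at the existing three-month interview, and keep hospital records as confirmation.
2. At each follow-up, record whether the participant or a proxy answered, so that a sensitivity analysis by respondent type is possible. The present proxy provision can stay.

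If a fuller protocol already provides a calendar, naming it in Data collection is enough.

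Cost: a printed form, one extra data field, and a sentence or two in Data collection. No extra visit or staff is needed. Some calendars will come back incomplete, and keeping one is a small burden on participants or carers.

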### Sample size calculation

A sample of 162 participants will be required to detect a between-group difference of 3 secs for the five balance tests (assuming a standard deviation of 9, power = 80%, p = 0.05, correlation between baseline and follow-up measures 0.65 and 15% drop out rate). Data from a previous study [4] indicate that 3 secs is likely to be approximately 15% of discharge values and we consider an effect of this size to be a clinically worthwhile.

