**Methods/Design:**

A single centre, randomised controlled trial with concealed allocation, assessor blinding and intention-to-treat analysis. One hundred and sixty two patients admitted to the general rehabilitation ward at Bankstown-Lidcombe Hospital will be recruited. Eligible participants will have no medical contraindications to exercise and will be able to: fully weight bear; stand unaided independently for at least 30 seconds; and participate in group therapy sessions with minimal supervision.

Participants will be randomly allocated to an intervention group or usual-care control group. Both groups will receive standard rehabilitation intervention that includes physiotherapy mobility training and exercise for at least two hours on each week day. The intervention group will also receive six 1-hour circuit classes of supervised balance exercises designed to maximise the ability to make postural adjustments in standing, stepping and walking.

The primary outcome is balance. Balance will be assessed by measuring the total time the participant can stand unsupported in five different positions; feet apart, feet together, semi-tandem, tandem and single-leg-stance. Secondary outcomes include mobility, self reported physical functioning, falls and hospital readmissions. Performance on the outcome measures will be assessed before randomisation and at two-weeks and three-months after randomisation by physiotherapists unaware of intervention group allocation.

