## Methods/Design

### Design

A single centre, randomised controlled trial with concealed allocation, assessor blinding and intention to treat analysis with three month follow up will be conducted among 162 rehabilitation inpatients. Figure 1 gives an overview of the study design.

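### The sample size of 162 is the number needed with no losses; with the stated 15% drop-out, power for a 3-second difference is about 73%, not 80%

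*Protocol article*

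**What the plan says.** The Sample size calculation section of the protocol article states that "A sample of 162 participants will be required to detect a between-group difference of 3 secs for the five balance tests". The assumptions follow in brackets: an SD of 9, 80% power, p = 0.05, and "correlation between baseline and follow-up measures 0.65 and 15% drop out rate". The drop-out rate is thus presented as one of the inputs that produced 162. The section adds that a 3-second difference is considered large enough to matter clinically.

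Two other places show that 162 is the number entering the trial, not the number completing it. The abstract (Methods/Design) says "One hundred and sixty two patients admitted to the general rehabilitation ward at Bankstown-Lidcombe Hospital will be recruited", and the Design section says the trial "will be conducted among 162 rehabilitation inpatients".

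The Primary outcome section names balance at two weeks and at three months. The Statistical analysis section plans ANCOVA with the baseline value as covariate at these follow-ups, which matches the use of a baseline-to-follow-up correlation in the calculation.

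**The concern.** Every quantity needed to check the calculation is printed apart from sidedness and allocation ratio, so the figure can be reworked directly. The rework gives 162 to 164 before any allowance for drop-out, which means the 15% is listed but appears not to have been applied.

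This is the trial's only statement of power, and it concerns the primary outcome. If losses occur at the assumed rate, the chance of missing a true 3-second effect is about 27% instead of the declared 20%. A reader who takes the printed 80% at face value would give a null result more weight against a 3-second effect than it deserves. The validity of the estimate and the type I error are not affected.

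**Working it through.** **Inputs.** From Sample size calculation: difference 3 s, SD 9 s, power 80%, significance level 0.05, baseline-to-follow-up correlation r = 0.65, drop-out 15%. From Statistical analysis: ANCOVA adjusting for baseline. Assumed: a two-sided test (not stated) and 1:1 allocation (two groups, blocks of four and six, no ratio given). Normal quantiles: 1.960 and 0.8416.

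**Step 1: number with outcome data.**

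- Residual SD = 9 × √(1 − 0.65²) = 9 × √0.5775 = 6.839 s.
- n per group = 2 × (1.960 + 0.8416)² × 81 × 0.5775 / 3² = 81.59.
- Total = 163.2, or 164 with each group rounded up. A t-based calculation gives 166.

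The plan's figure is 162 = 2 × 81, which is 81.59 per group rounded down. The stated number is reproduced to about 1%, but only with no loss.

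**Step 2: allow for 15% drop-out.**

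- 163.2 / 0.85 = 192.0.
- 164 / 0.85 = 192.9, so 193, or 194 for equal groups.
- The shortcut of multiplying by 1.15 gives 164 × 1.15 = 188.6, so 189.

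None of these is near 162. The shortfall against 192 is 30 participants, or 30/162 = 19% of the stated sample.

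**Step 3: power of 162 recruited.**

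| Analysed | Standard error of the difference | 3 / SE | Power (normal) | Power (t) |
|---|---|---|---|---|
| 162 (no loss) | 6.839 × √(2/81) = 1.075 | 2.79 | 79.7% | 79.2% |
| 138 (162 × 0.85 = 137.7) | 6.839 × √(2/69) = 1.164 | 2.576 | Φ(2.576 − 1.960) = 73.1% | 72.5% |

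With 138 analysed, the difference detectable with 80% power is (1.960 + 0.8416) × 1.164 = 3.26 s.

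**Step 4: could another reading give 162 after drop-out?**

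| Reading | Total before loss | Total after 15% loss |
|---|---|---|
| ANCOVA, one-sided 0.05 | 128.5 (130 rounded up) | 151 to 153 |
| Change score, two-sided | 198 | 233 |
| Change score, one-sided | 156 | 184 |
| No baseline adjustment, two-sided | 284 | 335 |
| Variance factor (1 − r) in place of (1 − r²), two-sided | 100 | 118 |
| Mean of both follow-ups, correlation between them 0.65 (assumed) | 114 | 135 |
| Mean of both follow-ups, correlation between them 0.82 (assumed) | 137.75 | 162.06 |

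For the last two rows the variance is 81 × [(1 + ρ)/2 − 0.65²], where ρ is the correlation between the two follow-ups. The last row is the only one that reaches 162, and it needs a value of ρ that the article does not give.

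**Step 5: could rounded inputs explain it?** Taking the most favourable values that would round to those printed (SD 8.5, r = 0.655), the total is 4 × 7.849 × 72.25 × 0.5710 / 9 = 143.9, and 143.9 / 0.85 = 169. For 138 analysed to give 80% power, the correlation would have to be about 0.715 with SD 9, or the SD about 8.28 with r = 0.65.

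**The case against.** The strongest counter-argument is that the primary outcome covers two time points, so the calculation might have been made for the average of both follow-ups. With a correlation of about 0.82 between them, that does give 162 after 15% drop-out. It cannot be ruled out as the origin of the number. However, the sample size section mentions no such correlation and no averaging, and the Statistical analysis section describes differences at the two follow-ups, not a mean of them. The no-loss reading uses only printed inputs and conventional assumptions. How 162 arose therefore remains an inference. That the printed inputs and planned ANCOVA do not yield 162 after 15% loss does not depend on it.

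Second, sidedness is not stated. Under a one-sided 5% test, 138 analysed participants would give 82.4% power and the 80% claim would be met. But a one-sided calculation would have produced 151 to 153 as the required number, and nothing in the article suggests a one-sided test. Two-sided is the usual reading, and it remains an assumption.

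Third, the 73% applies only if the full 15% is lost. One drop-out rate is given for two primary time points, without saying which it refers to. If losses at two weeks are smaller, power there lies between 73% and just under 80%. This is a fair qualification, and the power figure should be stated conditionally.

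Fourth, the practical effect is modest: the detectable difference moves from 3.0 to 3.26 s. That limits the damage but does not make the sentence correct.

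**Conclusion.** The concern holds. On the article's own inputs, with a two-sided 5% test, equal groups and ANCOVA at a single follow-up, 162 is the number required with complete data, not the number to recruit when 15% will be lost. At the assumed loss, about 138 are analysed, power for 3 s is 73.1% (72.5% t-based), and the type II error is about 27%, roughly one third above the declared 20%. The difference detectable with 80% power is 3.26 s. With no loss at all, 162 gives 79.7%. Neither a one-sided test nor rounding of the inputs reproduces 162 after drop-out; averaging the two follow-ups does so only with an unstated correlation of about 0.82. No adjustment for having two primary time points enters these figures.

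**What to change.** Correct the sentence in Sample size calculation. One suitable wording:

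> Recruiting 162 participants and losing 15% leaves about 138 for analysis. With an SD of 9 s, a baseline-to-follow-up correlation of 0.65 and a two-sided 5% test, this gives about 73% power to detect 3 s, or 80% power to detect about 3.3 s.

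Alternatively, keep 162 but say that it assumes complete outcome data (79.7% power) and remove drop-out from the list of assumptions. Either way, state the sidedness of the test. If the calculation was in fact made for the mean of the two follow-ups, say so and give the correlation used; the analysis section would then have to match.

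The abstract and the Design section give 162 without a power figure, so they need no change as long as 162 stays the recruitment target.

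The cost is a less favourable stated power and no extra patients. If the sponsor prefers to keep 80% power for 3 s after 15% loss, the target becomes about 193 (194 for equal groups), some 31 or 32 more participants, and every mention of 162 would need updating.

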### Statistical analysis

Between group differences in the primary outcome and secondary measures at the two week and three month follow-ups will be analysed using ANCOVA models where baseline values are entered as covariates. Dichotomous outcomes will be analysed via logistic regression models. Primary analyses will use an intention-to-treat approach. A secondary per protocol analysis will be undertaken using data from those who participated in at least three of the six intervention sessions.

## Discussion

This trial will provide essential information to guide evidence-based physiotherapy at the study site as well as across other rehabilitation inpatient settings. Specifically, it will identify whether the addition of a two-week circuit-class balance program improves balance, mobility and function among rehabilitation inpatients. Decreased balance and its subsequent effects such as falls decreased mobility and functional within the inpatient setting is a significant and costly issue for the health system. Despite this cost there has been very little research to date examining the effectiveness of exercise programs designed to improve balance in this setting.

The exercise approach in this standing balance circuit class have been designed using evidence from systematic reviews and randomised trials in other settings in which they have been demonstrated to improve balance and decrease falls. The ratio of up to 8 patients for two therapists ensures that it is a cost-efficient program and feasible in a rehabilitation setting. The eligibility criteria for the circuit class have been designed to ensure that the program is appropriate for a broad range of rehabilitation inpatients. The two-week intervention period, though short, has been designed to fit in with usual practice.

If shown to be effective, this balance program has the potential to improve the balance, mobility and function of future rehabilitation inpatients both at the study site and across other similar settings where this program is implemented. These physical function improvements have potential to transfer to an improved quality of life for patients and their families and carers. In addition, gains in balance and function may also reduce fall rates, which would confer significant benefit to the wider community in terms of reducing the financial burden associated with falls.
